#### Descriptive analyses at baseline

Descriptive statistics of baseline demographic and potential confounding variables at the patient, GP, and practice level will be presented (Table 5). These statistics will allow assessment of the comparability of intervention groups at baseline, and provide descriptive information about the study sample.

**Table 5 T5:** Baseline characteristics at patient, GP, and practice level (presented by intervention group)

**Patient level**	**GP level**	**Practice level**
*Cohort 1**	Age (years) (mean, SD)	No. GPs per practice (mean, SD)
Age (years) (mean, SD)	Sex (no., % female)	Rural practices (no., %)
Sex (no., % female)	No. of years since graduated from medical school (mean, SD)	Estimated total number of patients on the practice’s books (mean, SD)
Suspected cognitive impairment (no., %)	Country of medical training (Australia or overseas) (no., % Australia)	Practice nurse available (no., %)
		Involved in undertaking health assessments for people aged ≥75 years (no., %)
Cognitive assessment using MMSE (no., %)	Yrs. practised in Aust. if overseas medical training (mean, SD)	
		Undertakes full assessment or part (in combination with GP) (no., %full)
*Cohort 2**	GP registrar (no., %)	Involved in other aged care activities (no., %)
Age (years) (mean, SD)	Fellow of RACGP (no., %)	Other health practitioners work in the practice (specialist, allied health) (no., %)
Sex (no., % female)	Member of GP Division in their region (no., %)	Practice formally involved in training GP registrars (no., %)
Cognitive assessment using MMSE (no., %)	Hours spent per week in clinical practice (mean, SD)	Practice services residential care facilities (no., %)
Depression assessment using validated scale (no., %)	No. patients seen per week (mean, SD)	Method of billing (bulk bill or co-payment) (no., %bulk bill)
	Percentage of patients over 70 (mean, SD)	
		Age of practice (years) (mean, SD)
Referral to CDAMS or specialist (no., %)	Special interest in dementia (no., %)	Ownership (corporate or privately owned) (no., %corporate)
Referral for CT scan (no., %)	Special interest in aged care (no., %)	
	Self-report of adherence to recommended behaviours (mean, SD)	
	Intention to adhere to recommended behaviours (mean, SD)	
	Behavioural constructs for primary outcomes (mean, SD)	

^*^Cohort 1: Active patients aged 70 years and older at baseline. Cohort 2: Active patients aged 70 years and older in whom the GP suspects cognitive impairment at baseline.

#### Primary analyses

Marginal models using generalised estimating equations (GEEs) will be fitted for binary outcomes (using a logit link function) to estimate the effectiveness of the intervention. These models appropriately account for the correlation of responses within practice. We will assume an exchangeable correlation structure (where responses from the same practice are assumed to be equally correlated [35,61]) and use robust variance estimation (which yield valid standard errors of the intervention effect even if the within-cluster correlation structure has been misspecified [62,63]). Generalised estimating equations do not constrain ICCs to be positive; however, in the context of this trial, the likely explanation for a negative ICC is sampling variability, and not a true underlying negative ICC [35,64]. Therefore, in the event that the ICC from a particular analysis is negative, we will estimate the intervention effect using ordinary logistic regression, which will yield conservative estimates of standard errors.

The measure of intervention effect arising from the above models is an odds ratio. To aid interpretation, we plan to also present risk differences [65]. Risk differences will be calculated from marginal probabilities estimated from the fitted models [66]. Confidence intervals for the risk differences will be calculated using bootstrap methods, appropriately allowing for the clustered structure of the data.

Linear mixed models (LMM) will be fitted for continuous outcomes to estimate the effectiveness of the intervention, allowing for clustering with a random practice effect [67]. Continuous outcomes will only be measured at the level of the GP (self-report measures, intention, and behavioural constructs) and there are likely to be few practices with multiple GPs. In circumstances where there are a small proportion of clusters with multiple observations, LMM have been shown to perform slightly better than GEEs [68]. For skewed continuous outcomes, model-based standard errors will be compared with those obtained from bootstrapping.

Our primary analyses of outcomes will include adjustment for the stratification variables (*e*.*g*., geographical location of the practice, number of GPs per practice) and pre-specified potential confounding variables (Figure 3). The potential confounders have been selected through discussion with the investigators and examination of the confounders adjusted for in other similar implementation trials (*e*.*g*., [16,30]). All pre-specified confounders will be included in the models even when no baseline imbalance exists, since confounder selection strategies based on observed data (*e*.*g*., selecting confounders using preliminary statistical tests) result in models with poor statistical properties (*e*.*g*., incorrect type I error rates) [69-72]. If there are outcomes with limited data or events, we will only adjust for the stratification variables and, where appropriate, the baseline of the outcome variable (*e*.*g*., self-report measures, intention, and behavioural constructs). For each outcome, the estimate of intervention effect and its 95% CI will be provided. For primary outcomes, we plan to provide estimates of ICCs and their 95% CI.

**Figure 3 F3:**
[figure not shown]
Potential confounding variables adjusted for in the primary analyses.

Regression diagnostics will be used to assess the influence of outliers on estimates of intervention effect and for analysing residuals. No adjustment will be made for multiple testing. All tests will be two-sided and carried out at the 5% level of significance.

#### Secondary analyses

GEEs fitted to binary outcomes yield unbiased estimates of intervention effect only when data are missing completely at random [73]. As noted previously (in the ‘Analysis subsets’ section), empty clusters arising from practices or GPs withdrawing post randomisation but prior to extraction of patient data may occur, and this may introduce bias. We will attempt to examine the potential impact of empty clusters on the intervention effects for the primary outcomes using weights to allow for patterns of ‘missingness’ [74]. Weights will be created based on proxy measures of clinical behaviour for the key recommendations (*e*.*g*., self-report adherence to cognitive assessment using MMSE, intention to adhere to cognitive assessment using MMSE).

Two inclusion criteria used to define cohort 2 (patients with suspected cognitive impairment) are based on use of the MMSE in the baseline period. If GPs suspect cognitive impairment, patients should receive further assessments using the MMSE, regardless of whether they have been previously assessed. The rate of MMSE assessment is likely to be higher in patients who have received a previous MMSE, since their GP is already more likely to adhere to this recommendation. Consequently, an MMSE assessment in the baseline period may modify the intervention effect for the primary outcome of cognitive assessment using MMSE. We will examine this by fitting a model that includes an interaction term between the intervention group and an administration of the MMSE in the baseline period.

For the primary outcomes, we plan to undertake a per-protocol analysis to estimate the effect of the intervention for the subgroup of GPs who comply with the intervention. Compliance to the intervention is defined as attendance at the workshop.

We plan to undertake explanatory analyses for the primary outcomes to examine if intervention effects are explained by our hypothesized mediators of practitioner behaviour (Figure 2) [75-78]. These explanatory analyses will form a separate publication.

In the IRIS trial, some behaviours will be measured both objectively (through medical records) and subjectively (self-report and behavioural simulation). When objective measures are available, we will examine the predictive validity of the subjective measures; this will aid in interpretation of the subjective measures and contribute evidence of their measurement properties.

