**Methods:**

The design is a parallel cluster randomised trial, with clusters being general practices. We aim to recruit 60 practices per group. Practices will be randomised to the intervention and control groups using restricted randomisation. Patients meeting the inclusion criteria, and GPs’ detection and diagnosis behaviours directed toward these patients, will be identified and measured via an electronic search of the medical records nine months after the start of the intervention. Practitioners in the control group will receive a printed copy of the guideline. In addition to receipt of the printed guideline, practitioners in the intervention group will be invited to participate in an interactive, opinion leader-led, educational face-to-face workshop. The theory-informed intervention aims to address identified barriers to and enablers of implementation of recommendations. Researchers responsible for identifying the cohort of patients with suspected cognitive impairment, and their detection and diagnosis outcomes, will be blind to group allocation.

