### Interventions

#### Control group

The control group will receive a printed copy of the SIGN guideline for the management of patients with dementia [3].

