##### Mediators of GP behaviour

For the two key recommendations (undertaking a formal assessment for cognitive impairment and for depression), potential mediators of GP behaviour include measures of behavioural constructs (*e*.*g*., emotion, knowledge, skills, and social influences) (Table 3). These mediators reflect the barriers and enablers that were identified in phase I of this project (through interviews with GPs), and were targeted through the intervention components. We include measures of intention to adhere to the two key recommendations, since intention in many theories is considered the most immediate predictor of behaviour [45], and we hypothesise that intention will mediate the relationship between GPs’ motivation and behaviour. If the intervention is effective, we posit that differences in these mediators between groups will be observed. Figure 2 displays the causal pathway demonstrating the hypothesised relationship between the intervention, mediators and behaviour. Examination of the effects of the intervention along the causal pathway has been restricted to the primary outcomes to limit respondent burden.

**Table 3 T3:** Behavioural construct domains (hypothesised mediators of GP behaviour)

**Domains**	**Domain definitions **[27]** (adapted from Michie *****et al*****. **[40]**)**	**Domain measured for behaviour**	
		Cognitive assessment^1^	Depression assessment^2^
*Motivation*			
Intention^3^	A conscious decision to perform a behaviour or a resolve to act in a certain way	✓	✓
Beliefs about capabilities	Acceptance of the truth, reality or validity about an ability, talent or facility that a person can put to constructive use	✓	✓
Beliefs about consequences	Acceptance of the truth, reality or validity about outcomes of a behaviour in a given situation	✓	✓
Emotion	A complex reaction pattern, involving experiential, behavioural and physiological elements, by which the individual attempts to deal with a personally significant matter or event	✓	✓
*Capability*			
Knowledge	An awareness of the existence of something	✓	✓
Skills	An ability or proficiency acquired through practice	✓	✓
Memory, attention and decision processes	The ability to retain information, focus selectively on aspects of the environment, and choose between two or more alternatives	✗	✓
*Opportunity*			

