### Sample size

The primary outcomes of the IRIS trial include cognitive assessment using MMSE and depression assessment using a validated scale in patients with suspected cognitive impairment (cohort 2). The trial has been powered to detect a difference of 15% in rates of the behaviours between groups (assuming control group rates of 50%). Using sample size formula (2) of Eldridge *et al*. [55] and assuming, on average 20 patients per practice are identified, with a coefficient of variation in practice size of 0.7, and an intra-cluster correlation of 0.10, 45 practices per group will be sufficient to detect the 15% increase in recommended behaviours with 90% power (two-sided significance level of 5%). Allowing for 25% attrition in practices, we aim to recruit 60 practices per group. Justifications of the parameters used in the sample size calculation are available in Additional file 2 – IRIS sample size calculations.

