### Effectiveness analyses

#### Analysis subsets

Intention-to-treat (ITT) analyses are generally recommended in randomised trials for the primary reason of preserving the benefits of randomisation; namely, maintaining the comparability of the intervention groups in known and unknown prognostic factors [56]. In addition, it has been argued that ITT analyses compared with other analysis strategies (*e*.*g*., per-protocol) are more appropriate for pragmatic trials since they provide estimates of intervention effect that are more reflective of what would be observed if the intervention was implemented in routine clinical practice [57-59].

While requirements of an ideal ITT analysis (including compliance with the randomised intervention, no missing responses, and follow-up on all participants [57]) have been established for patient randomised trials, only recently has there been more detailed discussion of the definition and application of ITT analyses in C-RTs [60]. In C-RTs with adequate allocation concealment, comparability of intervention groups can be compromised not only through missing responses and loss to follow-up (as occurs in patient randomised trials), but also through recruitment of participants occurring post randomisation. Furthermore, loss to follow-up in cluster trials can occur at different levels (clusters and patients) because of the hierarchical structure of the design.

In the IRIS trial, retrospective identification of eligible participants will be undertaken (post randomisation) by researchers blind to group allocation, so the potential for selection bias will be minimised. In addition, bias arising from missing responses and loss to follow-up at the patient level will be minimal, since data will be extracted through the CAT on all eligible patients. However, practices and GPs may withdraw prior to data being extracted on their patients, resulting in empty clusters. A full application of the ITT principle in this circumstance would require the empty clusters to be accounted for in the analysis. Accounting for empty clusters would require strong assumptions to be made about patient characteristics and outcomes based on GP or cluster characteristics.

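### The secondary per-protocol analysis defines compliance by workshop attendance, which only intervention GPs can have, so on its ordinary reading it does not identify the effect among compliers

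*Protocol article*

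**What the plan says.** The primary analysis is a modified ITT: clusters, GPs and patients are analysed as randomised, whatever they received, without imputation (Analysis subsets). For the primary outcomes, the Secondary analyses section adds that "we plan to undertake a per-protocol analysis to estimate the effect of the intervention for the subgroup of GPs who comply with the intervention". The definition follows at once: "Compliance to the intervention is defined as attendance at the workshop".

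Attendance is voluntary. According to the Methods paragraph of the abstract, "practitioners in the intervention group will be invited to participate in an interactive, opinion leader-led, educational face-to-face workshop". The comparator has no workshop: "The control group will receive a printed copy of the SIGN guideline" (Control group).

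The Analysis subsets section gives the reason for preferring ITT as preserving randomisation, that is, "maintaining the comparability of the intervention groups in known and unknown prognostic factors". Covariate adjustment is described for the primary analyses: "Our primary analyses of outcomes will include adjustment for the stratification variables", together with pre-specified confounders listed in a figure that is not shown. The per-protocol paragraph says nothing about adjustment and names neither a comparator nor an estimator.

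**The concern.** The stated target is an effect among compliers, but the compliance rule can be applied in one arm only. A per-protocol analysis ordinarily leaves out intervention GPs who did not attend. No control GP can be classed as a would-be attender, so all controls remain. GPs who took up an invitation are then compared with a mixture of GPs who would and would not have done so.

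The protocol gives reason to expect that the two kinds of GP differ on the outcome. It has motivation acting on behaviour through intention and notes that "intention in many theories is considered the most immediate predictor of behaviour" (Mediators of GP behaviour). If motivation also governs who comes to a workshop, it confounds this contrast. The analysis could then suggest a benefit where there is none, or overstate a small one. Tests are at the 5% level with no multiplicity adjustment, so a low per-protocol p-value could be read as further support for the workshop.

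There is also a mismatch with the design. The Trial design section counts diffusion among GPs in the same practice as part of the effect under evaluation. Splitting by individual attendance sets aside non-attending colleagues who may have been exposed.

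**Working it through.** **1. The plan's own figure.** From Sample size: 50% versus 65%, two-sided 5%, 90% power, 20 patients per practice, coefficient of variation of practice size 0.7, intra-cluster correlation 0.10.

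- Patients per arm under individual randomisation: 227.
- Design effect = 1 + ((0.7² + 1) × 20 − 1) × 0.10 = 1 + 28.8 × 0.10 = 3.88.
- Practices per arm = 227 × 3.88 / 20 = 44.04, rounded up to 45. With 25% attrition, 45 / 0.75 = 60.

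The stated figures reproduce. They serve here only as a yardstick (15 points) and for precision.

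**2. Bias of attenders versus all controls when the workshop does nothing.** Let *a* be the attendance share, r_A and r_N the untreated rates in would-be attenders and non-attenders, and *g* = r_A − r_N. By randomisation the control rate is

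r = a·r_A + (1 − a)·r_N,

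so the expected contrast is

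r_A − r = (1 − a)(r_A − r_N) = (1 − a)·g.

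Both *a* and *g* are **assumptions**, since the documents give neither. The formula also assumes no covariate adjustment. The last column is the chance of rejecting at a nominal 5%. It takes a 50% control rate, 45 practices per arm, 20 patients per practice, design effect 3.88 and a × 900 attender patients.

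| a | g (points) | Bias (1 − a)·g (points) | Approx. false-positive rate |
|---|---|---|---|
| 0.8 | 5 | 1.0 | 5.5% |
| 0.7 | 10 | 3.0 | 9% |
| 0.6 | 15 | 6.0 | 20% |

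Over a wider grid (a = 0.5 to 0.9, g = 5 to 20 points) the bias runs from 0.1 × 5 = 0.5 to 0.5 × 20 = 10 points, and the false-positive rate from about 5.1% to 42%. If *g* is negative, the bias has the same size and the opposite sign.

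**3. The alternative under the same null.** A complier-average effect is the ITT risk difference divided by *a*. If the true ITT difference is 0, the target is 0 / a = 0 whatever the value of *g*, provided assignment has no effect without attendance. Treating *a* as known, its standard error is the ITT standard error divided by *a*. Intervals are therefore wider by 1 / 0.8 = 1.25 to 1 / 0.6 = 1.67 times for attendance of 80% to 60%.

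**The case against.** The strongest reply is that two sentences in an article give a target and a definition but no comparator, estimator or covariates, and such detail is commonly left to an analysis plan. The stated target is a complier effect, which a complier-average analysis would serve. It is true that the comparator is inferred. A reader should not take it as stated that non-attenders are dropped and all controls kept. What remains is that the article does name a per-protocol method and a one-arm rule, and together they do not deliver the named target. That is a fault in what is stated, not an omission.

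A reader might also infer that the trial's main conclusion is at risk. The documents do not support this. The modified ITT is primary, the per-protocol analysis is listed as secondary, and no decision rests on it.

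Nor do the documents show that the bias must favour the workshop. GPs in both arms volunteered for a trial that offered a possible dementia workshop, which may narrow the gap. One workshop date is given, so absence may reflect availability or distance. Limited training and confidence are listed as barriers, so less skilled GPs might be the ones to attend.

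Finally, Table 5 records GP intention, self-reported adherence and special interest in dementia. Adjusting for these could reduce the bias, and the article does not rule it out. It does not commit to it for this analysis either, and unmeasured motivation would remain.

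The alternative has weaknesses of its own. Control guidelines were sent in November 2012, about five months after the workshop of June 23, and no date is given for the intervention arm. Assignment could therefore act through guideline timing as well as through the invitation. A practice-level definition also changes the target.

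**Conclusion.** The concern holds as a structural point about a secondary analysis. Compliance is defined by an event after randomisation that only one arm can experience. The ordinary per-protocol contrast therefore gives up the comparability for which the protocol itself favours ITT, and it does not identify the effect among compliers.

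The illustrative size of 1 to 6 points depends on assumed attendance of 60–80%, an assumed gap of 5–15 points, no covariate adjustment and the inferred comparator. It would be small if attendance were near complete. An upward direction is plausible but not established. The primary modified ITT analysis stands. The change is worth making, but the point does not count against the main result.

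**What to change.** Make the complier estimate a complier-average causal effect for each primary outcome:

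- randomised group as the instrument for practice-level attendance, meaning that at least one participating GP attended, which fits the within-practice diffusion described under Trial design;
- two-stage estimation on the risk-difference scale, with practice-clustered robust standard errors and the primary-analysis covariates;
- a statement that the target is then complying practices, not complying GPs;
- a statement that assignment is assumed to have no effect without attendance, whether through the invitation or through any difference between arms in when the printed guideline arrived. Reporting when the intervention arm received it would let readers judge this.

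If an attenders-versus-controls contrast is kept, adjust it for baseline GP intention, self-reported adherence and special interest in dementia. Name the comparator, and label the result exploratory and non-randomised.

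The cost is a change of wording and one extra model. Attendance is already needed for the planned analysis, the listed GP variables are already in Table 5, and risk differences are already planned. Intervals will be wider than for ITT. Patient-level data collection had only just begun when the article was submitted, so the change could be made before results were known.
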